### Data collection timepoints

We will evaluate participants at baseline, at the end of the intervention period (10 weeks), and 6 months after the randomisation. We will perform the evaluation through videoconference, telephone contact, or using an online questionnaire (e-mail or text message), according to the participant’s preference.

### Evaluation and data collection

#### Blinding

The outcome assessors will be blinded to the allocation of participants in the study groups. To assess the effectiveness of blinding, the assessors will be asked at the end of the study to guess which group they believe each participant was allocated to. However, due to the nature of the interventions, it will not be possible to blind the participants or the researchers responsible for delivering the interventions.

#### Characteristics of the sample

We will collect age, gender, body mass, height, marital status, profession/work, level of education, cognition [45], self-assessment of general health status, and drug and non-drug treatment [46].

#### Implementation outcomes

Implementation outcomes will be used according to Proctor’s conceptual model of implementation research [36] (Fig. 3) and will be evaluated at different levels of analysis: (1) organisation (public health managers) and/or setting (health professionals, community health agents, primary healthcare unit’ leaders or other health servers involved in the implementation process); (2) end-users (participants from the SUS with chronic musculoskeletal pain); (3) individual providers (evaluators and intervention executing team).

**Fig. 3 Fig3:**
[figure not shown]
Adaptation of Proctor’s conceptual model of implementation research

The primary implementation outcomes will be cost-effectiveness, adoption, and acceptability (satisfaction using a numerical scale from 0 to 100). Primary and secondary implementation outcomes are described below and summarized in Table 1.*Acceptability* will be analysed from the perspective of the organisation through a focus group, from the perspective of end-users through an individual qualitative interview about satisfaction with the intervention, and by a numerical scale from 0 to 100 on how satisfied they were in participating in the intervention. The acceptability of the implementation will also be evaluated by the Acceptability of Intervention Measure (AIM) [47] in organisations and end-users. The AIM has four questions with a Likert scale from 1 (completely disagree) to 5 (completely agree), and the mean of the score will be used (1 to 5). Higher scores indicate greater acceptability [47].*Appropriateness* will be analysed from the end-users’ perspective regarding the perception of the appropriateness of each component of the *EducaDor* programme about their health condition through an adapted questionnaire [48]. This questionnaire will assess the degree to which participants agree with a series of statements about the intervention, on a Likert scale from 1 (totally disagree) to 4 (totally agree). The appropriateness of the implementation will also be evaluated by the Intervention Appropriateness Measure (IAM) [47] in the organisation and end-users. The IAM score is the same as the AIM.*Feasibility* will be evaluated from the perspective of the organisation and individual providers through a focus group, and the Feasibility of Intervention Measure (FIM) [47] will be used in participants, organisations and individual providers. The FIM score is the same as the AIM and AIM.*Adoption* will be analysed by the percentage of acceptance of public health users to participate in the *EducaDor* programme referred from primary healthcare. We will contact by telephone those public health users who refuse to participate by inviting them to an individual qualitative interview to identify barriers to engagement in the *EducaDor* programme.*Fidelity* will be evaluated by an independent pain specialist ([name]), who will randomly select 10% of the recorded meetings and evaluate the intervention providers in relation to the fidelity of the intervention manuals with the content and quality of the meetings in a qualitative individual interview.The adherence of participants with the *EducaDor* programme will be measured by the frequency rate in synchronous meetings; self-rated performance of proposed homework on a numerical scale from 0 to 10 during the intervention period; and by exercise adherence scale (EARS-Br) [49].*Penetration* will be analysed descriptively from the rate of public health users referred from each primary healthcare unit.*Sustainability* will be evaluated by a focus group with public health managers after the presentation of the results of the study to discuss the maintenance of the *EducaDor* programme, and by a response rate of synchronous group users and reasons for discontinuity of the programme through an individual qualitative interview.*Costs* will be estimated from the SUS and societal perspectives in a time horizon of 6 months. The SUS costs will include the intervention costs and healthcare utilization costs covered by SUS. The intervention costs will be determined by preparation, video recording, development and editing, maintenance and support technology costs, monitoring data costs and staff, training health professionals and project management costs, number and duration of phone calls and the number of text messages sent to participants. The e-book and asynchronous intervention costs will be diluted in 10 years. The healthcare utilization costs covered by SUS will include prescribed drugs, medical consultations, physiotherapy-based care, visits to specialists, diagnostic exams, emergency services and hospitalisation. The societal costs will include the SUS costs, private healthcare costs, patient costs (out-of-pocket expenses with unprescribed drugs, complementary costs, and transportation costs), and lost productivity costs (related to absenteeism). The quantities of resource utilization will be identified by the participants in a self-rated diary cost that will be provided at baseline and an assessor will collect this information by telephone every 3 months. The healthcare utilization costs covered by SUS will be valued using the Brazilian standard costs [50]. Patient costs will be valued using the out-of-pocket expenses reported by patients. Private transportation will be valued by the price of Brazilian gasoline per kilometre and public transportation by the reference price of Guarapuava city. The lost productivity costs will be estimated from the hours of absenteeism to work (paid and unpaid) through a questionnaire, and evaluated according to the Human Capital Approach and will be valued using gender-specific price weights [50].

**Table 1 Tab1:** Implementation outcomes

**Outcomes**	**Level of analysis**	**Indicators**		**Data Collection Tool**		**Time of data collection**
**Acceptability**	Organisation	Acceptability of the implementation		Qualitative interview and Acceptability of Intervention Measure (AIM)		Post-implementation
	Participants	Satisfaction with the intervention		Qualitative interview and 0 to 100 points scale and AIM		Post-implementation
**Appropriateness**	Participants	Are the components of the online pain science education programme appropriate for the health condition?		Qualitative interview, Intervention Appropriateness Measure (IAM) and an adapted questionnaire used by Liao et al. (2020)		Post-implementation
	Organisation	If intervention is appropriate for the public health condition		Intervention Appropriateness Measure (IAM)		Post-implementation
**Feasibility**	Participants	Feasibility of the intervention		Feasibility of Intervention Measure (FIM)		Post-implementation
	Organisation	Feasibility of the implementation		Qualitative interview and FIM		Post-implementation
	Individual providers	Feasibility of the implementation		Qualitative interview and FIM		Post-implementation
**Adoption**	Participants	Enrolled participants being contacted		Own domain database		During implementation
		Burden (reasons for not taking part)		Qualitative interview during triage		Pre-baseline
**Fidelity**	Creator of the intervention	10% of taped sessions of the intervention group were randomly selected and reviewed by an expert panel, against the full detailed intervention manuals for adherence and quality		Qualitative interview		Post-implementation
	Participants	Number of participants that adhered to the intervention		Frequency during intervention		During implementation
		Self-rated performing the proposed activities at home for 10 weeks and the 6-month of follow-up		Adherence to the proposed homework (0 to 10 points scale); and the exercise adherence scale (EARS-Br)		Post-implementation
**Penetration**	Organisation	Which primary healthcare units referred users with musculoskeletal pain for intervention?		Health regulation data and/or digital health record		During and post-implementation
**Sustainability**	Organisation	Do you think this project will be sustainable over time?		Qualitative interview		Post-implementation
	Participants	Indicator of drop in the response rate of the synchronous group		Own domain database		During implementation
		Burden (reasons for discontinuation or dropping out)		Qualitative interview		During implementation
**Costs**	Participants	Self-rated costs for the treatment of chronic pain		Diary of cost		During and post-implementation
	Organisation	Costs of public healthcare		Domain database and health regulation data		Post-implementation
	Individual providers	Costs of the intervention		Survey		Post-implementation
	Researchers team	Cost-effectiveness		Economic evaluation (incremental cost-effectiveness ratio – ICER—of the three strategies of the intervention)		Post-implementation
		Cost-utility		Economic evaluation (measured by the EQ-5D-3L to calculate quality-of-life-adjusted life years)		Post-implementation

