However, the literature is scarce in reporting the process and the outcomes of the implementation of interventions in digital models [20, 30]. Furthermore, evidence of chronic musculoskeletal pain clinical guidelines is derived largely from research on high-income economies [30]. Thus, Implementation research to bring the chronic musculoskeletal pain clinical guidelines into policy and ‘real-world’ practice in low- and middle-income countries is urgently needed.

The implementation of an online pain science education programme in Brazil can provide helpful information for low- and middle-income countries.

Therefore, the primary aim of this study is to investigate the implementation outcomes and effectiveness of three implementation strategies of an online pain science education programme in the Brazilian public health system of Guarapuava city. The second aim is to determine the cost-effectiveness of such strategies.

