### Procedures and randomisation

Individuals referred to the EducaDor programme will first be contacted by a researcher ([name]; [name]) via an electronic videoconferencing system at the scheduled consultation. During this initial contact, the researcher will screen the participant for eligibility and provide information about the EducaDor programme, as well as the name of the referred physiotherapy centre. Eligible participants will receive a link to an online consent form via email or text message, which they can accept to participate. Once the consent form is accepted, one researcher will conduct the baseline assessment, and another researcher will randomly assign the participant to one of the intervention groups.

Participants included in the study will receive physiotherapy-based care and the *EducaDor* programme as per randomisation into three different modes of delivery: (1) synchronous online group; (2) asynchronous videos group; or (3) interactive e-book group. Although the three groups have the interactive e-book, the synchronous online group and the asynchronous videos group receive additional types of digital content that are accessible to participants who cannot read and/or write in Portuguese. Then, the first step of randomisation will be done for participants who cannot read and/or write in Portuguese into (1) synchronous online group or (2) asynchronous videos group. The second step of randomisation will include all other eligible participants into the three different modes of delivery: (1) synchronous online group; (2) asynchronous videos group; or (3) interactive e-book group.

One researcher ([name]) will perform a stratified block randomization within the five physiotherapy centres accredited at SUS in the city, at the ratio of 1:1, using Excel software. The randomised list will be under the custody and confidentiality of the researcher ([name]). One week before the start of the *EducaDor* programme, one researcher ([name]) will send a list of participants to the researchers responsible for the interventions ([name], [name], [name], and [name]). The intervention researchers will then contact the participants to explain the intervention according to group allocation.

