#### Quantitative data analysis

For continuous variables, we will calculate statistics of central tendency and dispersion, such as means and, standard deviation. For categorical variables, we will describe frequencies and absolute numbers. Normality will be investigated by visual inspection of histograms. The baseline characteristics of the participants and implementation outcomes will be calculated using descriptive statistics. The differences between groups and the 95% confidence interval will be calculated using mixed models. The fixed effect term will be composed of dummy variables indicating groups, and follow-up time-points, that is, 10 weeks and 6 months after baseline, and the interaction terms composed of group and time. The estimates will be adjusted for any potential differences that might exist at the baseline. The random effect term will be composed of: (1) a correlated random intercept and slope varying the intercept for the five physiotherapy clusters and varying the slope for time points; and (2) a correlated random intercept and slope varying the intercept for repeated measurements within each cluster and varying the slope for time-points [69].

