To evaluate the robustness of the results, two exploratory sensitivity analyses will be performed. The first sensitivity analysis will be performed by excluding the total costs of the e-book and the asynchronous video development and editing. The second sensitivity analysis will be performed considering only patients with more than 75% of adoption of the intervention. The economic evaluation will be conducted at RStudio.

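### Adoption is settled before randomisation and cannot compare the three delivery modes; satisfaction can, but the protocol states only a descriptive analysis for it

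*Protocol article*

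**What the plan says.** Under Implementation outcomes the article states: "The primary implementation outcomes will be cost-effectiveness, adoption, and acceptability (satisfaction using a numerical scale from 0 to 100"). Adoption "will be analysed by the percentage of acceptance of public health users to participate in the" EducaDor programme, among users referred from primary healthcare. Table 1 gives its indicator as enrolment among those contacted, collected during implementation. The reasons for declining come from a "Qualitative interview during triage", timed before baseline.

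Procedures and randomisation sets the order of events: "Once the consent form is accepted, one researcher will conduct the baseline assessment, and another researcher will randomly assign the participant" to a group. After that, "The intervention researchers will then contact the participants to explain the intervention according to group allocation".

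Table 1 schedules the 0 to 100 satisfaction score, from participants, after implementation.

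Quantitative data analysis says: "The baseline characteristics of the participants and implementation outcomes will be calculated using descriptive statistics". It then describes mixed models for group differences with 95% CIs. These have 10-week and 6-month time points, group-by-time terms and adjustment for baseline differences. The outcomes they cover are not named.

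The second sensitivity analysis in Economic evaluation is performed "considering only patients with more than 75% of adoption of the intervention".

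**The concern.** The Background says that "the primary aim of this study is to investigate the implementation outcomes and effectiveness of three implementation strategies" of the programme. In a hybrid type III trial the implementation outcomes lead, so readers will look to the three primary ones for evidence on which mode of delivery to choose. Only cost-effectiveness has an explicit between-group plan, in Economic evaluation.

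For adoption, the risk is that a pooled percentage is reported as if it said something about the strategies, or that an arm contrast is improvised later. For satisfaction, the risk is three arm means with no estimated difference or interval. Those raw means would also describe different populations: participants who cannot read or write in Portuguese are randomised only between the synchronous and video arms, so the e-book arm contains none of them. A descriptive table would mix that difference with any effect of the delivery mode.

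**Working it through.** **The plan's own figure.** Neither adoption nor satisfaction has a sample-size or precision figure to reproduce. The only calculation is for pain: 80 per group before corrections and 105 after. With a difference of 1.0, SD 2.3, two-sided alpha 0.05 (sidedness assumed) and 80% power, the standard two-means formula gives 84 per group, and power at 80 is 78.5%. The inflation 80 × 1.3 = 104 is close to 105. This point does not depend on that calculation; it uses only the 105 per arm and the 30% loss.

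**Adoption, from the order of events.**
1. Referral, first contact and screening, online consent, baseline assessment, allocation, explanation of the allocated mode (Procedures and randomisation).
2. The numerator of adoption is complete at consent. Those who decline are never allocated, so no arm has its own denominator.
3. Table 1's indicator is still an enrolment ratio. Collecting it while implementation is under way does not move any one user's acceptance to after allocation.
4. The result is one pooled proportion, and a between-arm difference is undefined.
5. The pooled proportion can be estimated well. The protocol gives no acceptance rate, so assume p between 30% and 90% with 315 enrolled. Users approached: N = 315/p. Half-width of the 95% CI: 1.96 × √(p(1 − p)/N).

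| Assumed p | N | 95% CI half-width |
|---|---|---|
| 30% | 1050 | 2.8 points |
| 50% | 630 | 3.9 points |
| 70% | 450 | 4.2 points |
| 90% | 350 | 3.1 points |

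**The 75% threshold.** Acceptance is yes or no for each user, and every randomised participant has accepted. Under the stated definition, a restriction to more than 75% adoption has no per-patient quantity to act on.

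**Satisfaction.** It is collected after randomisation from participants in all arms, so a difference is estimable.
- Evaluable per arm: 105 × 0.70 = 73.5.
- 95% CI half-width for a pairwise difference: 1.96 × √(2/73.5) = 0.32 SD. With no loss it is 1.96 × √(2/105) = 0.27 SD.
- Detectable pairwise difference at 80% power, two-sided 0.05: (1.96 + 0.84) × √(2/73) = 0.46 SD. With no loss it is 0.39 SD.
- The protocol gives no SD for the score. For an assumed SD of 15 to 30 points, 0.46 SD is about 7 to 14 points.

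**The case against.** The strongest objection concerns satisfaction. A reader might infer that neither outcome can compare the strategies. The documents do not support that for satisfaction, because the design allows the comparison and only the analysis text falls short. A reader might also infer that satisfaction is measured once and so cannot enter the group-by-time model. The article does not say so. Table 1 gives the same timing label to homework adherence, which it describes as covering 10 weeks and the 6-month follow-up, and the schedule figure is not available. Adjustment for baseline differences could mean covariates, not a baseline satisfaction score. The sentence on mixed models excludes no outcome, and a condensed article may leave the model for each outcome to an analysis plan. All of this stands. What remains is that the article does state an analysis for implementation outcomes, and that analysis is descriptive.

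A programme-level primary outcome is also legitimate. One hypothesis in the Discussion is that the programme can be implemented at all, and an acceptance percentage informs that. It would therefore go too far to say that the primary aim is unanswered: cost-effectiveness and pain both have between-group plans. The objection does not give adoption an arm-specific value.

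The 75% wording is probably loose language for adherence, in an exploratory analysis. That makes it a minor correction, though one still needed because it reuses the name of a primary outcome.

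Finally, attendance at the first synchronous meeting might seem a natural primary measure of adoption by arm. It is not a like-for-like measure. In the video and e-book arms that meeting introduces the materials and may be individual; in the synchronous arm it is the first of ten intervention sessions.

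**Conclusion.** The point holds for adoption without qualification: as defined, it cannot compare the delivery modes, and more recruitment does not change that. It also cannot supply the per-patient threshold in the sensitivity analysis.

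For satisfaction the point is narrower. The comparison is available by design, with a 95% CI half-width of roughly 0.27 to 0.32 SD, but the protocol assigns implementation outcomes descriptive statistics and does not state that the mixed model applies to this one.

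The satisfaction figures assume equal arms of 105, up to 30% loss, no allowance for the three pairwise comparisons, and no correlation within centres or meeting groups. The adoption intervals assume 315 enrolled and an acceptance rate that the protocol does not give. The conclusion on adoption needs none of these assumptions; it follows from the order of consent and allocation.

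**What to change.** 1. **Adoption.** Label it as a pre-randomisation, whole-programme descriptive outcome. State its denominator (referred or contacted), report it with a 95% CI, and draw no between-arm conclusion from it. If uptake by arm is wanted, add it as a secondary outcome among all randomised participants, and note that the first meeting plays a different role in the synchronous arm.
2. **Satisfaction.** State that pairwise between-arm differences in the 0 to 100 score will be estimated with 95% CIs by linear regression on arm, centre and literacy step. The literacy term is needed because participants who cannot read or write are never allocated to the e-book arm; contrasts with that arm then rest on the participants who could have been allocated to it.
3. **Sensitivity analysis in Economic evaluation.** Replace adoption with an adherence or exposure measure already collected, and state the threshold on that measure's own scale. The homework self-rating (0 to 10) and EARS-Br are candidates. Attendance at weekly synchronous meetings serves only one arm.

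The cost is a short amendment and slightly more analysis, with no new visit or instrument. The price is that adoption is no longer presented as comparing the strategies. The registry entry, which was not available here, should be checked for consistency.

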#### Fidelity of intervention delivery

The interventions will be conducted by four physiotherapy students ([name], [name], [name], and [name]) from Universidade Estadual do Centro-Oeste (UNICENTRO/Brazil). The team will receive 30 h of training regarding the interventions before the beginning of the *EducaDor* programme. The chief researcher of the study ([name]), who has 18 years of physiotherapy experience, will audit the online interventions once every month. To maintain the fidelity of the intervention delivery, the researchers will follow a structured manual of the *EducaDor* programme. All synchronous meetings will be recorded for further evaluation of the implementation fidelity.

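### Provider delivery is to be judged from recordings against a manual, but the only tool named is a qualitative interview, so delivery fidelity will not be quantified

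*Protocol article*

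**What the plan says.** All references are to the protocol article.

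- **Implementation outcomes, Fidelity.** The assessor is one independent pain specialist, "who will randomly select 10% of the recorded meetings and evaluate the intervention providers". The evaluation concerns "fidelity of the intervention manuals with the content and quality of the meetings in a qualitative individual interview".
- **Table 1, Fidelity, first row.** The indicator is 10% of taped sessions, "randomly selected and reviewed by an expert panel, against the full detailed intervention manuals for adherence and quality". The data collection tool in that row is a qualitative interview, the timing is post-implementation, and the level of analysis is the creator of the intervention.
- **Fidelity of intervention delivery.** Four physiotherapy students deliver the programme after 30 hours of training, and "the researchers will follow a structured manual of the *EducaDor* programme". "All synchronous meetings will be recorded for further evaluation of the implementation fidelity". The chief researcher audits the online interventions monthly; no score or output of the audit is named.
- **Quantitative data analysis.** "The baseline characteristics of the participants and implementation outcomes will be calculated using descriptive statistics".
- **Other Fidelity measures (text and Table 1).** These are attendance at synchronous meetings, self-rated homework on a 0 to 10 scale, and the EARS-Br. Under Missing data, an EARS-Br score of at least 17 also defines compliers for the CACE analysis.

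**The concern.** The indicator and the tool do not match. The indicator asks how far recorded meetings followed a manual. That can be observed component by component. An interview held after implementation collects a judgement about delivery. It does not record which components were delivered in a given meeting, and it produces nothing that the planned descriptive statistics can summarise.

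This goes beyond detail left to a fuller document, because the article states the tool, twice and consistently. For acceptability, appropriateness and feasibility, Table 1 lists a numeric instrument (AIM, IAM or FIM) beside or instead of the interview. In the provider-fidelity row the interview stands alone.

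At stake is the reading of the synchronous arm. Four students run the meetings, and the Implementation strategies section allows adaptations throughout the process, so delivery may vary between providers or drift over time. If the synchronous arm performs no better than the others, readers will ask how much of the manual was delivered. The plan provides a narrative answer and no amount.

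**Working it through.** **Which Fidelity measures concern the provider.** The article states no fidelity figure, so there is none to reproduce. Its measures are:

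| Measure | Whose behaviour | Form |
|---|---|---|
| Review of 10% of recordings against the manual | Provider | Qualitative interview |
| Monthly audit | Provider | No output named |
| Attendance; number who adhered | Participant | Numeric |
| Homework 0 to 10 | Participant | Numeric |
| EARS-Br | Participant | Numeric, also used for CACE |

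No provider measure is numeric.

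**How many recordings the 10% sample holds.** The article gives 105 participants per arm (Sample size estimation), groups of up to 12 and 10 weekly meetings (EducaDor programme). It does not give the number of groups, so group size is assumed.

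- Groups of 12: 105/12 = 8.75, so 9 groups; 9 × 10 = 90 meetings; 10% = 9 recordings.
- Groups of 12, also counting one recorded group orientation meeting per 12 participants in the video and e-book arms: 90 + 2 × 9 = 108 meetings; 10% = 10.8, about 11. About 2 of these would be orientation meetings (10% of 18).
- Groups of 8: 105/8 = 13.1, so 14 groups; 14 × 10 = 140 meetings; 10% = 14 recordings.

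**What a checklist would give overall.** Assume k = 9 recordings, m = 10 or 20 components per meeting, 80% delivered, and a within-meeting correlation (ICC) of 0.1 or 0.2. None of these inputs is in the article.

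Half-width = 1.96 × √(0.8 × 0.2 × DE / (k × m)), with DE = 1 + (m − 1) × ICC.

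| m | ICC | DE | Half-width (points) |
|---|---|---|---|
| 10 | 0.1 | 1.9 | 1.96 × √(0.16 × 1.9/90) = 11.4 |
| 10 | 0.2 | 2.8 | 1.96 × √(0.16 × 2.8/90) = 13.8 |
| 20 | 0.1 | 2.9 | 1.96 × √(0.16 × 2.9/180) = 10.0 |
| 20 | 0.2 | 4.8 | 1.96 × √(0.16 × 4.8/180) = 12.8 |

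With 14 recordings each value is multiplied by √(9/14) = 0.80, giving about 8 to 11 points. The formula ignores clustering by provider and treats 9 to 14 clusters as a large sample, so these widths are somewhat optimistic.

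**By provider.** Nine recordings over four providers is 9/4 = 2.25 each. A quarter of the data doubles the half-width, to about 20 to 28 points, which is not informative.

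**Whole-meeting pass/fail instead of components.** Exact 95% intervals are 66% to 100% for 9 of 9 passing, 40% to 97% for 7 of 9, and 49% to 95% for 11 of 14. Scoring components uses the same recordings better.

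**The case against.** A reader might infer that the trial will have no fidelity figure at all. The documents do not support that. Attendance, homework and EARS-Br are numeric and sit under Fidelity, so the planned descriptive statistics do have Fidelity data to work on. Only the provider side lacks a number.

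A reader might also infer that the trial could not tell a mode that failed from one that was badly delivered. That goes too far as well. Recordings are still reviewed against the manual for adherence and quality, and there is training and a monthly audit. Poor delivery could be noticed and described. What is missing is its extent.

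Three further objections carry weight:

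- This is a mixed-methods implementation trial that uses qualitative tools on purpose, and the interview may simply be how the reviewer's assessment is elicited. A rating form may exist in a fuller protocol or in the manual, neither of which is shown. The published text and Table 1 would still name the wrong tool, or an incomplete one.
- The video and e-book arms use fixed content plus one live meeting. Session fidelity is therefore not a common yardstick for the three modes.
- With so few recordings, a checklist cannot measure variation between the four providers with useful precision. This limits the remedy but does not remove the case for an overall figure.

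**Conclusion.** The point holds in a limited form. For provider delivery, the indicator and the only named tool disagree in both the text and Table 1, and no quantitative delivery result is specified. The issue falls mainly on the synchronous arm. Fidelity is not among the primary implementation outcomes (cost-effectiveness, adoption and acceptability), and the primary effectiveness outcome, pain intensity, is unaffected. This is a worthwhile, low-cost improvement and not a threat to the trial's main conclusions.

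The attainable gain is one overall percentage with a 95% half-width of roughly 10 to 14 points with 9 recordings. That size rests wholly on assumed group size, component count, delivery rate and within-meeting correlation.

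The same Table 1 row conflicts with the text on the assessor. The text has one independent pain specialist; the table has an expert panel, at the level of the intervention's creator. Who rates, and whether that rater is independent, is unclear as written.

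**What to change.** - Have the same reviewer score each sampled recording on a checklist taken from the existing manual. Mark each component as delivered, partly delivered or not delivered, and add one fixed quality rating.
- Report percent delivered overall, with an interval that allows for clustering by recording.
- By provider and by meeting type (weekly synchronous meeting or orientation session), give counts only, without intervals.
- Keep the qualitative interview as a supplement, to explain the scores.
- Correct the tool in Table 1 and in the Fidelity text, and make the two agree on who assesses.

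The cost is drafting one form and some extra reviewer time. The recordings and the review are already planned. If the recordings are kept, scoring can be done after delivery has ended.
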